### Data collection

2.7

Data of age, sex, duration of SFN, use of pain medication, pain intensity, disability, and SFN-related diagnostic (such as skin biopsy outcome and outcome of quantitative sensory testing) outcomes will be collected. Only principal investigator and the coordinating researcher will have access to the data.

The study protocol is reported in accordance with the SPIRIT guidelines [Standard Protocol items: Recommendations for Interventional Trials (78)].

### Data management

2.8

All data will be entered into a web-based trial management system by members of the research team. All data will be coded with unique study number. The research team will have a list showing codes and patients’ names, separately from the study database. Only the study coordinator will have access to this list, and the main database.

#### Amendments

2.8.1

Amendments, or changes of the research protocol after IRB approval, will be reported to the METC that approved the research protocol.

### Sample size calculation

2.9

Based on previous experience with single-case experimental designs in chronic pain, 10 participants provide sufficient power to answer our hypothesis that rehabilitation based on biopsychosocial principles is effective to decrease disability and improving QOL (79). Therefore, at least 10 participants need to complete the study. In case a participant withdraws, a new participant will be included. Studies that tested the statistical properties of the randomization test used in this type of design showed that type I error probability of the randomization test was maintained at an acceptable level (48, 80, 81). SCED studies have multiple measurements, resulting in a large effect size and great power (82). Each participant is equal to one experiment. And each experiment will be repeated at least for 10 times. The variation of the treatment starting point will show if a treatment is effective, and that the significant outcome is related to the treatment modality. With a kind of meta-analysis, it is possible to combine all the *p*-values (of each participant). Therefore, this study design is a powerful method due to the multiple measurements and the number of participants (10 repetitions). Compared to RCT studies, more than 100 participants will be included, with only a couple of measurements per participant. Contrary to SCEDs, daily and multiple measurements will be gathered, and therefore, a sample size of 10 is enough to analyze the data with a sufficient outcome. The total number of participants and permutations is not related to the power of the design, however, calculation of the p-value is possible by dividing the total number of permutations (83). The aim of this study is to observe if a multidisciplinary rehabilitation treatment modality is suitable and effective in the treatment of psychosocial factors in SFN. certain treatment modalities are used as care as usual in different chronic pain conditions, in which there is always a selection between different treatment options.

### Statistical analysis

2.10

The baseline characteristics will be presented in means ± standard deviation, medians (interquartile range) or percentages, as appropriate, including age, sex, duration of SFN, use of pain medication, pain intensity, disability, and SFN-related diagnostic (such as skin biopsy outcome and outcome of quantitative sensory testing). The outcome of the questionnaires will be analyzed using SPSS (Version 27). Normality assumptions will be checked with the Shapiro–Wilk test. Normally distributed treatment effects variables will be analyzed with the paired student’s t-test. Non-normally distributed treatment effects variable will be analyzed with the paired Wilcoxon test.

The analysis of the daily dairy data will be conducted with the Shiny SCDA, which is a web application to analyze SCED studies (51, 84). Shiny SCDA, a web-based application, has been developed to easily analyze and investigate intervention effects of the SCED data at an individual level, but also to combine the SCED data through multilevel modeling and randomization tests, which create a higher internal validity (48). Randomization test are based on the random determination of the moments of phase change points to test a null hypothesis about treatment effects (85). Randomization tests have the advantage of being valid for single-case experiments without making distributional assumptions, of being easy to apply and of being extremely versatile for even the most complex single-case design.

Each SCED will be individually analyzed, but we will use *p*-value combining (of the 10 SCEDs in this project), which has the advantages that it is broadly applicable and that it is distribution-free without converting the scores to ranks or signs. The following schedule will be used to investigate when treatment effects occur during the study period:

The baseline data (phase A) will be compared with the intervention, post-intervention and follow-up data (phase B + C + D).The intervention data (phase B) will be compared with the baseline data (phase B) and with the post-intervention and the follow-up data (phase C + D).The post-intervention data (phase C) will be compared with the baseline data (phase A) and with the follow-up data (phase D).The follow-up data will be compared with the baseline data (phase A) and the intervention data (phase B).

A *p*-value of 0.05 will be set.

It is important that the various periods [ea. (A), (B), (C), (D)] show a substantial amount of non-overlapping data. Nonoverlapping data of pairs (NAP) is an indicator of differences between the different phases in the treatment schedule. We do not expect that there will be an immediate effect from the start of treatment, however, we expect that there will be a gradual positive effect.

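### For the diary data, a significant combined p-value supports benefit in at least one participant, not overall effectiveness; a pooled signed effect should be added

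*Protocol article*

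**What the plan says.** All references are to the protocol article.

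- **Sample size calculation** states the aim in directional and general terms: "10 participants provide sufficient power to answer our hypothesis that rehabilitation based on biopsychosocial principles is effective to decrease disability". It argues that the varied start of treatment will show whether treatment works, and continues: "With a kind of meta-analysis, it is possible to combine all the" individual p-values. From this it concludes that the design is powerful with ten replications.
- **Daily measures** says the diary serves the primary and secondary outcomes.
- **Statistical analysis** analyses each diary series by a randomization test. For the group it commits to p-value "combining (of the 10 SCEDs in this project), which has the advantages that it is broadly applicable". On the threshold it says only that a p-"value of 0.05 will be set". The null hypothesis is described without a sign.
- **Statistical analysis** also says the software can be used to analyse individuals, "but also to combine the SCED data through multilevel modeling and randomization tests". This describes what the software offers. No model or pooled estimate is committed to.
- The questionnaires, which carry PDI, SFN-RODS and SF-12, get a paired t-test or a paired Wilcoxon test in the same section. NAP is named as an indicator of differences between phases, with no pooling across participants.

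**The concern.** The hypothesis is that the treatment, taken as a whole, lowers disability and raises quality of life. The group test chosen for the diary data answers a narrower question: is there evidence against the statement that nobody's scores changed? Rejecting that statement is compatible with a clear effect in some participants and none in the rest. It carries no effect size. If the individual tests are not pointed towards benefit, it carries no sign either.

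This matters because the diary analysis is the part that uses the randomized start point, and the article rests its causal argument on that feature. A significant combined p-value could then be read as showing the treatment to be effective in SFN generally, with no pooled diary estimate or interval to support or temper that reading. Direction also needs active setting. In Table 2 some items improve downwards (pain, difficulty of the activity) and others upwards (cheerfulness, score for one's life). Several scheduled contrasts, such as C against D, have no stated expected sign.

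**Working it through.** **Inputs.** From the article: 10 participants; threshold 0.05, sidedness not given; baseline length 10 to 30 days. If every whole day can be drawn, there are 30 − 10 + 1 = 21 start points, so the smallest individual p is 1/21 = 0.0476. The article names no combining rule, so three common ones are shown. It gives no power, effect size or SD, so there is no stated figure to reproduce.

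**Formulas**, for k = 10 p-values:
- Edgington: S = Σp; P = (1/10!) Σ_j (−1)^j C(10,j) (S − j)^10, for j from 0 to the integer part of S.
- Fisher: X = −2 Σ ln p, referred to chi-square with 20 df.
- Stouffer: Z = Σz / √10.

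**Step 1. One-sided tests, five clear improvers, five showing nothing** (p = 1/21 five times, 0.50 five times).
- Edgington: S = 5/21 + 2.5 = 2.738. P = (2.738^10 − 10 × 1.738^10 + 45 × 0.738^10) / 3,628,800 ≈ (23,685 − 2,516 + 2) / 3,628,800 = 0.0058.
- Fisher: X = 2 × (5 × 3.045 + 5 × 0.693) = 37.4, P = 0.011.
- Stouffer: Z = 5 × 1.668 / 3.162 = 2.64, P = 0.004.

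All three rules are well below 0.05 with half the sample showing no effect. This does not depend on sidedness being left open.

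**Step 2. Two-sided tests, every participant at 1/21.** Edgington: S = 10/21 = 0.476, P = 0.476^10 / 10! = 1.7 × 10⁻¹⁰. Stouffer gives 6.6 × 10⁻⁸ and Fisher 5.2 × 10⁻⁶. The inputs carry no sign, so these values are the same for ten improvers and for five improvers with five worseners.

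**Step 3. One-sided towards benefit, five at 1/21 and five at 20/21.** Edgington: S = 5, P = 0.50. Stouffer gives 0.50 and Fisher 0.056. None reaches 0.05, though Fisher lets the opposing results offset each other far less than the other two.

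**Step 4. Simulation of A against all later days.** 1,000 runs per scenario, 10 participants, 21 start days and 56 + 28 = 84 later days. AR(1) correlation 0.3, an immediate shift and the shift sizes are assumptions. Share of trials with combined p ≤ 0.05:

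| Scenario | Tests | Edgington | Stouffer | Fisher |
|---|---|---|---|---|
| All 10 improve by 1 SD | two-sided | 85% | 80% | 66% |
| 5 improve, 5 worsen by 1 SD | two-sided | 86% | 80% | 65% |
| 5 improve, 5 worsen by 1 SD | one-sided | 1.0% | 0.8% | 0.9% |
| All 10 improve by 0.5 SD | two-sided | 29% | 22% | 12% |
| 5 improve, 5 worsen by 0.5 SD | two-sided | 29% | 22% | 13% |
| No effect | two-sided | 2.4% | 1.7% | 0.3% |
| No effect | one-sided | 3.0% | 1.6% | 0.7% |

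With no effect, rejection stays below 5% under every rule. The problem is therefore what a rejection means, not an inflated type I error.

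**The case against.** A reader might infer that the trial's whole group conclusion rests on combined p-values, that it could declare success while half the participants worsen, and that it yields no average effect. The article does not support that reading, for four reasons.

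- **Other group analysis.** PDI, SFN-RODS and SF-12, the named main endpoints, get paired tests. These are signed, and the t-test gives a mean change. With five better and five worse by a like amount they would tend not to reject.
- **Sidedness.** The article does not say the randomization tests are two-sided. The hypothesis is directional, and a gradual positive effect is expected. An analysis plan that is not shown may settle the direction, so the figures of about 86% are conditional.
- **Visibility.** Each series is analysed individually and NAP is named, so participants who worsened could be seen. No success rule says that a combined p ≤ 0.05 alone means effective.
- **Scenario.** Nothing in the article suggests that half the participants would worsen by 1 SD, and the simulation uses an immediate shift although a gradual one is expected.

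All of this stands and limits the point to the diary data. It does not remove it. The paired tests are before-after comparisons without a control and do not use the randomized start, so they do not supply a pooled effect from the randomized part of the design. Step 1 holds with one-sided tests, so fixing the direction elsewhere would not cure it.

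There is also a fair case for keeping p-value combining, because it needs no distributional assumption. Replacing it with a multilevel model fitted to 10 participants across three treatment modules would be a trade-off, not a correction.

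**Conclusion.** The point holds for the diary data only. The article commits to p-value combining as the group step and leans on it for a directional, general claim, but a significant result supports only an effect in at least one participant. The size: five participants at 1/21 and five at 0.50 give a combined p of 0.004 to 0.011, depending on the rule. This rests on 21 eligible start days.

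Loss of sign is a second, conditional weakness. It arises only if the individual tests are two-sided, and benefit-directed tests reduce it to about 1% or less in the simulated mixed case. It is not established that the trial would call the treatment effective with half its participants worse, or that the trial as a whole lacks an average effect.

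**What to change.** Keep p-value combining and make three changes to the diary analysis.

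1. Compute each individual p-value in the direction of benefit before combining, with that direction fixed in advance for each diary item and each contrast.
2. Alongside it, report the average A versus B+C+D effect with a 95% confidence interval, for example from the multilevel option of the software already chosen, and the numbers of participants who improved and who worsened.
3. Word a significant combined p-value as evidence of benefit in at least one participant. Claim overall effectiveness only if the pooled effect supports it.

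The cost is some wording and one more model run. With 10 participants the interval will be wide, and the conclusion the trial can draw will be more modest.

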### Study design

2.1

The design is a randomized replicated sequential single-case experimental ABCD design (SCED) with multiple measurements (48) (see Figure 1). Each participant will enrol in the baseline period, completing daily measurements with an electronic diary (A). The randomization in the baseline period will define the length of the baseline period (ranging between 10 to 30 days), increasing the internal validity and credibility (49, 50). By the randomization, the start point of the treatment module (date) will be determined (B). Therefore, the start point differs among participants (48, 51, 52). The treatment module will have a duration of 8 or 10 weeks, independent of the treatment type (these logistics are a standard clinical procedure). Each participant will be evaluated by the treatment team according to their personalized goals after 4 weeks. The further treatment module will exist of a short- (4 weeks) or long (6 weeks) treatment module, which will be added to the previous 4 weeks. The content of the short- and long treatment module will not differ. The only difference is the duration between both treatment modules. The differences between the short- and long treatment module will not be analyzed, because that is not the main focus of this study. After the treatment module, a post-treatment of two weeks will follow (C). At last, the study will end with a period two weeks of follow-up (D). Before the start of each period, participants will complete a couple of questionnaires (see Non-daily measures). The length of the baseline period (A) will be randomized between 10–30 days and participants will complete daily measurements with an electronic diary in the baseline period (A), for 8–10 weeks in the treatment module (B), two weeks post-treatment (C) and two weeks at follow-up (D) (see Figure 1, see Daily measures). Before the start of each period, participants will complete a couple of questionnaires (see Non-daily measures). Randomization of the baseline period will occur according to the length of the baseline period (between 10 and 30 days) and the start of the treatment module (B), increasing the internal validity and credibility (49, 50).

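### The ten p-values to be combined can only be multiples of 1/21; under the usual continuous-p formulas the group test would be valid but conservative (true size 0.7-2.8% at a nominal 5%), and an exact or joint randomisation test removes this at no cost

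*Protocol article*

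**What the plan says.** Study design (2.1) fixes what is randomised: "The randomization in the baseline period will define the length of the baseline period (ranging between 10 to 30 days". The treatment start date follows from that draw.

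Sample size calculation (2.9) describes the individual p-value: "calculation of the p-value is possible by dividing the total number of permutations". The same sentence asserts that neither the number of participants nor the number of permutations bears on the power of the design. The section then relies on pooling: "With a kind of meta-analysis, it is possible to combine all the *p*-values (of each participant". From this, and from the repeated measurements, it concludes that ten participants are enough. It gives no effect size, autocorrelation or numeric power.

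Statistical analysis (2.10) makes the group step a commitment: "we will use *p*-value combining (of the 10 SCEDs in this project". The stated merit is that it is a method "which has the advantages that it is broadly applicable and that it is distribution-free without converting the scores to ranks or signs". The level follows: "A *p*-value of 0.05 will be set". Multilevel modelling and randomisation tests are mentioned as things the web application can do to combine data. The section closes by expecting a gradual effect rather than an immediate one.

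No combining rule or reference distribution is named anywhere.

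**The concern.** A randomisation p-value with 21 equally likely start dates takes only the values 1/21, 2/21, ..., 1. Its null mean is 22/42 = 0.524, not 0.5, and it cannot fall below 1/21 = 0.048. The usual combining rules (additive, Stouffer, Fisher) take each p-value to be continuous and uniform on 0-1. Applied to ten p-values on this grid, they reject too seldom.

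Combining is the group test the plan commits to for the diary data, and part of its argument that ten participants suffice. A test that nominally runs at 5% but in fact runs well below it gives up power that a trial of ten people can ill afford, and gains nothing the plan asked for. The point concerns the size of the combined test, not what one participant's test can reject.

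**Working it through.** **Inputs.** From the protocol: ten p-values; alpha 0.05; baseline 10-30 days; p formed by dividing by the number of permutations. Inferred: 30 - 10 + 1 = 21 start dates, if every whole day is admissible and equally likely. Under the null each p is then uniform on {1/21, ..., 21/21}, whether the individual test is one- or two-sided. The plan states no size or power figure to reproduce.

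**Additive rule.** The continuous reference is P(S ≤ s) = (1/10!) Σ (-1)^j C(10,j)(s - j)^10, summed over j from 0 to the integer part of s.
- At s = 73/21 = 3.476 it gives 0.0477; at 74/21 it gives 0.0533. The formula therefore rejects at 73/21 or less.
- The true probability of a sum of 73/21 or less, by exact convolution of ten discrete uniforms, is **2.79%**.
- On the exact null, P(sum ≤ 77/21) = **4.49%** and P(sum ≤ 78/21) = 5.02%, so the exact cutoff is 77/21 = 3.667.

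**Fisher.** The statistic -2 Σ ln p is referred to chi-square with 20 df, where each term should have mean 2. On the grid the mean term is (2/21)(21 ln 21 - ln 21!) = (2/21)(63.935 - 45.380) = 1.767, so the total averages 17.67 instead of 20. True size by simulation (4 million draws): **0.70%**.

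**Stouffer.** The sum of normal scores divided by √10 is referred to N(0,1). True size by simulation: **1.77%**.

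**Sensitivity to the inferred 21.** With fewer start dates the shortfall grows:

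| Start dates | Additive | Stouffer | Fisher |
|---|---|---|---|
| 21 | 2.79% | 1.77% | 0.70% |
| 19 | 2.61% | 1.60% | 0.56% |
| 15 | 2.14% | 1.18% | 0.31% |

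**Power.** The protocol gives no effect inputs, so these are assumptions: 3,000 simulated trials per setting, phase A against B + C + D, B = 56 days, C + D = 28 days, one-sided mean difference, lag-1 autocorrelation 0.3. The effect is either abrupt or rises linearly over 8 weeks. Each cell gives power with the continuous formula, then with the same statistic and an exact reference.

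| Effect | Additive | Stouffer | Fisher |
|---|---|---|---|
| Abrupt 0.25 SD | 15.3 / 20.2% | 10.6 / 21.3% | 4.9 / 20.3% |
| Abrupt 0.5 SD | 42.0 / 50.7% | 33.8 / 51.0% | 20.3 / 50.1% |
| Abrupt 0.75 SD | 69.6 / 76.2% | 61.9 / 76.0% | 44.4 / 74.9% |
| Abrupt 1 SD | 87.0 / 90.4% | 81.4 / 90.4% | 65.9 / 89.9% |
| Abrupt 2 SD | 99.8 / 99.9% | 99.3 / 99.6% | 98.3 / 99.9% |
| Gradual 1 SD | 4.8 / 7.0% | 3.1 / 7.8% | 1.3 / 7.7% |
| Gradual 2 SD | 6.0 / 9.1% | 4.1 / 10.1% | 1.6 / 9.7% |

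Across autocorrelations 0, 0.3 and 0.6, the largest abrupt-effect losses are 8.7 points (additive), 17.6 (Stouffer) and 32.5 (Fisher). Under gradual effects the losses are about 2-3, 3-7 and 4-8 points, and exact-reference power is about 5-11%.

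**Joint randomisation test.** In 12,000 null trials it rejected 5.1% (autocorrelation 0.3) and 5.2% (0.6) of the time. The Monte Carlo standard error is √(0.05 × 0.95/12,000) = 0.2 points, so both agree with 5%. In a companion simulation (abrupt shifts of 0.5, 0.75 and 1 SD, autocorrelation 0.3) its power was 52%, 80% and 94%, against 48%, 76% and 91% for the exact additive rule. That further gain comes from a different statistic and is not part of the discreteness correction.

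**The case against.** The strongest reply is that the plan never says it will use a continuous-p formula. A reader might infer from the arithmetic that this trial's group test does run at 0.7-2.8% and does lose up to 30 points of power. The document does not support that. It names no rule, and an exact or permutation reference would fit its emphasis on randomisation tests. A condensed article may also leave the rule to a fuller document. This stands: the loss is conditional.

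Three more replies also stand.
- The quoted sentence is not false. Combining remains distribution-free, and the type I error is below 0.05, not above it.
- The large power losses belong to abrupt shifts and mainly to Fisher's rule. The protocol expects a gradual effect, for which the loss is small in points and power is poor with either reference.
- The 1/21 grid applies only to comparisons resting on the randomised A-to-B start. The later phase changes have no randomised start of their own. The 77/21 cutoff is for exactly ten participants, while section 2.9 speaks of at least ten.

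What remains is not merely an unstated detail. All three usual formulas err in the same direction on this grid, the unstated choice moves the true size about fourfold (2.79/0.70 = 4.0), and a better test costs nothing. The assertion in 2.9 about permutations and power is also in the text and is wrong: fewer start dates lower the attained size of these combined tests, and the number of p-values combined affects power directly.

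**Conclusion.** The point holds as a conditional one. If the ten p-values are combined by a usual continuous-p formula, the nominal 5% group test is valid but conservative, with true size 2.8%, 1.8% or 0.7% depending on the rule. This rests on 21 equally likely start dates and ten participants, and applies to the A-to-B comparisons.

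The sizes are firm under those assumptions; the power cost is not. It ranges from nearly nothing for large abrupt shifts, through about 4-9 points (additive) to about 30 (Fisher) for mid-sized abrupt shifts, to about 2-8 points for a gradual rise. In the gradual case exact calibration alone does not rescue the test, since power stays at about 5-11%. The change is worth making as a free improvement. It does not show that the plan's conclusions would be invalid.

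**What to change.** For comparisons based on the randomised A-to-B start, name the group test and give it an exact reference. Either:

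1. **Joint randomisation test (preferred).** Take the mean over participants of the standardised phase difference. Compare it with its distribution when every participant's start date is redrawn independently from their possible dates, with at least 9,999 draws.
2. **Exact additive combining.** Keep the sum of p-values, but refer it to its exact discrete null for the actual number of participants and start dates. For 10 and 21, reject if the sum is 77/21 or less (size 4.5%); recompute the cutoff if either number differs.

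State the number of admissible start dates. In section 2.9, remove or correct the claim that the numbers of participants and permutations are unrelated to power.

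Cost: a few lines of code, possibly outside the web application, and two amended sentences. No new data and no change to the design.

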#### Treatment

2.2.3

Each treatment module will be provided by a treatment team consisting of the rehabilitation physician, a psychologist, and an occupational therapist or a physiotherapist, all of whom are experienced in each treatment module. One of the three treatment modalities will be chosen. Participants have to complete the treatment module to which they are allocated. Participants will only follow one treatment module. The treatment will continue for 8–10 weeks, with a twice a week a 1-h session. The duration will be determined by team members and the rehabilitation physician after the first phase of 4 weeks. During a team meeting, the team members will consider a short or long phase-2 based on the progress in the first phase (see Table 1).

**Table 1 tab1:** Overview and summary of the treatment modalities.

	Graded activity	Exposure *in vivo*	Acceptance and commitment therapy
Team meeting	Meeting 1: 4 weeks after start of the treatment module Meeting 2: the final treatment session Meeting 3: 6 weeks after the completion		
Duration (total)	8–10 weeks		
Treatment schedule	Phase 1: 8 sessions in total with 1-h/session According the progress in phase 1, the team members choose the duration of phase-2 (short or long) Phase 2-short: 8 sessions in total with 1-h/session Phase 2-long: 12 sessions in total with 1-h/session		
Therapist	Psychologist and physical- or occupational therapist		
Underlying paradigm	Operant conditioning	Inhibitory learning approach (classical conditioning)	Relational frame theory
Treatment aim	Increase activity tolerance and healthy behaviour	Modifying fear-related beliefs resulting in disability/restrictions	Increase psychological flexibility
Scientific evidence	Reduction of disability, pain catastrophizing and/or pain intensity in chronic low back pain and chronic neuropathic pain (39)	Reduction of disability and pain catastrophizing in complex regional pain syndrome type 1 and chronic back pain (5, 6)	Reduction of disability in chronic pain disorders (46, 47)
Selection based on	COPM	Outcome of PHODA	COPM

COPM; Canadian occupational performance measure; PHODA, photographic series of daily activities.

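### B vs C+D, C vs D and D vs B are listed under randomisation tests and p-value combining, but only the A-to-B date is randomised, so these three contrasts have no valid randomisation-test basis

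*Protocol article*

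**What the plan says.** **What is random.** Study design (2.1): "The randomization in the baseline period will define the length of the baseline period (ranging between 10 to 30 days"), and "By the randomization, the start point of the treatment module (date) will be determined (B"). No other date is drawn by lot.

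**What is not random.** Treatment (2.2.3), on the length of B: "the team members will consider a short or long phase-2 based on the progress in the first phase". This gives 8 or 10 weeks. Study design then says "After the treatment module, a post-treatment of two weeks will follow (C") and "At last, the study will end with a period two weeks of follow-up (D").

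**What the test rests on.** Statistical analysis (2.10): "Randomization test are based on the random determination of the moments of phase change points to test a null hypothesis about treatment effects". Sample size calculation (2.9) adds that "calculation of the p-value is possible by dividing the total number of permutations".

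**What is compared.** Section 2.10 announces p-value combining over the 10 participants, gives a schedule of comparisons meant to show when effects occur, and closes with a 0.05 threshold. The third item of the schedule reads "The post-intervention data (phase C) will be compared with the baseline data (phase A) and with the follow-up data (phase D"). One entry compares B with a baseline that is labelled phase B. Read as phase A, the list holds seven contrasts: A vs B+C+D, B vs A, B vs C+D, C vs A, C vs D, D vs A and D vs B. The last entry of each of the final three items matters here, because B vs C+D, C vs D and D vs B do not involve phase A.

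**The concern.** A randomisation test gets its p-value from the assignments that the design could have produced. If a change point was not drawn at random, the design supplies no alternatives to compare with the observed one. The assurance in section 2.9 that the test keeps the type I error acceptable cannot extend to such a change point.

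The three contrasts without phase A bear on whether anything changed when treatment ended and whether it lasted. A p-value below 0.05 there would look as well founded as the one for the start of treatment, but would rest on a reference set chosen by the analyst or the software. A gradual effect, which the end of section 2.10 expects, makes this worse: whole-phase means then differ between B and the later phases even if nothing happens when treatment stops.

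**Working it through.** The plan gives no figure for these contrasts that could be reproduced. The sample size of 10 comes with no effect size, variance or power.

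**1. Assignments the design allows.** Smallest p = 1 / number of possible assignments.

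| Change | How it is set | Possible assignments | Smallest p per participant |
|---|---|---|---|
| A to B | drawn, 10 to 30 days (any whole day: assumption) | 30 − 10 + 1 = 21 | 1/21 = 0.0476 |
| B to C | team decision on progress | 1 | 1 |
| C to D | fixed, two weeks after C starts | 1 | 1 |

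If all ten participants have p = 1, the combined p is also 1 (additive method of Edgington; assumed, as the article names none).

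**2. What an invented reference set does.** Simulation with 10 participants per trial, 400 trials per setting and no effect of any phase change. Assumptions: first-order autocorrelation 0, 0.3 or 0.6; no trend, or a steady improvement of 0.01 innovation SD per day; B of 56 or 70 days depending on simulated week-4 progress; one-sided mean difference; Edgington combining. Monte Carlo error near 5% is √(0.05 × 0.95 / 400) ≈ 1 percentage point. D vs B was not simulated.

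| Test | Rejection at 0.05, no trend (autocorrelation 0 / 0.3 / 0.6) | With trend |
|---|---|---|
| A vs B+C+D, true randomised start | 1.8% / 2.0% / 1.3% | 3.0% / 3.7% / 3.3% |
| B vs C+D, diary days shuffled | 3.7% / 6.2% / 12.5% | 100% / 99.0% / 82.5% |
| C vs D, diary days shuffled | 5.0% / 9.2% / 10.5% | 25.3% / 26.3% / 22.8% |
| B vs C+D, end of B treated as random within ±10 days | 1.3% / 0.7% / 1.0% | 3.0% / 1.8% / 0.5% |
| C vs D, change treated as random within ±7 days | 0.3% / 1.3% / 1.3% | 0.5% / 1.0% / 0.5% |

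The A-to-B test holds its level throughout. For the other contrasts the answer depends on which invented set is used. The trend result is no surprise: with B of 56 days and C+D of 28 days, the phase midpoints lie (56 + 28)/2 = 42 days apart, so the trend alone gives 0.01 × 42 = 0.42 SD.

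**3. Gradual effect and whole-phase means (assumed illustration).** Let a 1-SD effect rise linearly over 8 weeks and then stay flat, so that on day t of B it equals min(t/56, 1), with t = 0, 1, 2 and so on.

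- 8-week B: mean = 27.5/56 = 0.491, so C+D lies 1 − 0.491 = 0.51 SD above B.
- 10-week B: mean = (27.5 + 14)/70 = 0.593, so C+D lies 1 − 0.593 = 0.41 SD above B.
- Last two weeks of B only: for 8 weeks, mean = 48.5/56 = 0.866, a gap of 0.13 SD; for 10 weeks, mean = 1, a gap of 0.

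Nothing changes after treatment in any of these cases.

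**The case against.** **The article never assigns a randomisation test to a named contrast.** Section 2.10 also mentions multilevel modelling, and nonoverlap of all pairs (NAP) as an indicator of differences between phases. This stands in part. A reader might infer that the three contrasts have no valid basis of any kind; the documents do not support that, since a model-based or descriptive comparison remains open. But neither method is tied to these contrasts, and the list directly follows p-value combining.

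**C vs A and D vs A.** A reader might infer that these must lose their randomisation p-values too. That does not follow: both involve the randomised boundary. Neither was tested here, and what such a p-value can speak to is the start of B.

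**The team does not see the diary.** Section 2.3 says that neither researchers nor clinicians have access to these data during treatment, so it would be wrong to say that the length of B is chosen on the diary outcome. It is still chosen on clinical progress, not by lot. Progress is judged against personal goals, and the personal goal is also an item in the diary (2.2.2).

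**The whole schedule shifts with the random start.** Shifting it would test the start date, not the end of treatment. Diary data also stop after D, so later hypothetical schedules would lack data.

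**Inflation is not shown for the plan itself.** This is correct. The large error rates come from shuffling days, which the plan does not propose; with an assumed window around the change points there was no inflation. The simulation shows that the result depends on the invented set, not that the trial's error rate will be high.

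**Conclusion.** The point holds for three of the seven contrasts: B vs C+D, C vs D and D vs B have no valid randomisation-test basis under the protocol's own definition of the test. Their only design-based p-value is 1. This rests on the text alone. The count of 21 for the A-to-B change assumes that any whole day may be drawn.

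The gaps of 0.51 and 0.41 SD depend on an assumed effect shape and size. They show how a whole-phase comparison can mislead under any method without a trend term. A reader might infer that the plan would interpret such a gap as a post-treatment effect, but it states no such reading.

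The point should be fixed, but it does not undermine the trial. Section 2.9 ties efficacy to the varied starting point, and A vs B and A vs B+C+D keep a valid test. The PDI, SFN-RODS and SF-12 questionnaires are analysed separately with paired tests. What is affected is what the trial can say about when effects occur and whether they last.

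**What to change.** 1. State in section 2.10 that randomisation tests and p-value combining apply to contrasts at the randomised A-to-B change: A vs B and A vs B+C+D.
2. Report B vs C+D, C vs D and D vs B as multilevel-model contrasts with trend and autocorrelation terms and 95% confidence intervals, or as descriptive NAP with graphs. Label them non-randomised.
3. If C vs A and D vs A keep a randomisation p-value, say that it tests only the randomised start of B.
4. To judge durability, compare C and D with late B, for example its last two weeks, instead of the whole of B. In the illustration this cuts the spurious gap from 0.51 to 0.13 SD for an 8-week B and from 0.41 to 0 for a 10-week B. It does not remove the gap in every case, so the trend term is still needed.

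The cost is a change of analysis wording and fewer p-values. Data collection and the conduct of the trial stay as they are.
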